#### Primary objective and outcome measure

The primary objective is to confirm the improvement in the quality of life at 6 months following the implementation of a post-therapeutic support and rehabilitation program for women in complete remission from breast cancer in thermal resorts (PACThe program), in real-life conditions, regardless of their treatment or the interval between the end of treatment and the start of the program.

The primary outcomes is the change in SF-36 global score [3] between baseline and at 6 months.

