### Sample size

The main analysis consists in comparing the change in SF-36 global score at 6 months from baseline to the value obtained in the PACThe study control group (historical comparator). In the randomized PACThe study, the difference in SF-36 global score between the experimental and control groups was 2.2 points at baseline (*p* =.3), and 9.5 points at 6 months (effect size = 0.63, *p* <.001), with a difference between 6 months and baseline of 11.9 points in the experimental group, and 4.6 in the control group, and a standard deviation between 15 and 16.

To determine the number of subjects required, it is assumed that the variation between 6 months and inclusion in this study will be slightly lower than in the PACThe study: expected value of 10 points. It is also estimated that the variability of the scores obtained will be greater than that observed in the PACThe study. Thus, a sample size of 400 should allow us to show a reasonable effect size of 0.2 (alpha risk equal to 5% and 95% power, for a one-sample Student’s t-test), and compensate for an estimated 15–20% drop-out rate.

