### Statistical analysis

The main analysis consists of comparing the change in SF-36 global score [3] between 6 months and baseline with the value obtained in the PACThe control group (historical comparator) using a Student’s t-test (or a non-parametric test depending on the data distribution). All patients who will not respond to the questionnaires at 6 months will be excluded from the analysis.

The evolution of the SF-36 global score over time (repeated data) will be analysed using mixed-effects linear regression models, followed, in the event of a statistically significant result, by post-hoc pairwise comparisons at different time points, with correction for multiple comparisons).

Confidence interval estimates of observed effects (changes in measurements at different time points post-program vs. baseline) will be used for comparison with the effects observed in the PACThe study, as well as analysis in subgroups defined by age, menopausal status and type of anti-cancer treatment.

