Data will be remotely monitored regularly based on the status of the patients enrolled at the participating center. The monitoring will be performed by a clinical research associate mandated by the Coordonator. The objectives will be to ensure the proper conduct of the study in each center, and the recording of the data generated. The monitoring reports will ensure traceability.

Missing data will not be replaced (they will be managed through partial exclusion). In cases where there is a significant amount of missing data, an analysis will be conducted to assess their statistical nature and potential impact on the results. If deemed relevant, an appropriate imputation method will be suggested.

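### The primary test uses only women who return the 6-month questionnaire, with 15–20% loss expected; if women who benefit less reply less, the estimated change is too high

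*Protocol article*

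**What the plan says.** The primary outcome is the "change in SF-36 global score [3] between baseline and at 6 months" (Primary objective and outcome measure). The main analysis is a one-sample comparison of that change with the change in the control group of the earlier randomized PACThe trial (Sample size; Statistical analysis). That value is 4.6 points.

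For women without a 6-month form, the Statistical analysis section is explicit: "All patients who will not respond to the questionnaires at 6 months will be excluded from the analysis".

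The Sample size section states that 400 women will also "compensate for an estimated 15–20% drop-out rate". According to Intervention and participant timeline, the baseline and end-of-stay questionnaires are handed over at the resort, while the 6-, 12- and 18-month questionnaires are sent to the patient.

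Two other statements bear on the point:

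- The Statistical analysis section plans mixed-effects linear models for the evolution of the same score over time, but not as the main analysis.
- Data management and monitoring sets partial exclusion without replacement as the general rule. If much is missing, it promises an assessment of the nature and impact of the missing data, and adds: "If deemed relevant, an appropriate imputation method will be suggested". It fixes neither the amount that triggers this nor the method.

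**The concern.** The complete-case rule is stated outright, so this is not a detail left to a later document. Raising the number enrolled replaces lost precision, but it cannot make responders representative of the women who started the programme.

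The design is exposed to selection for two reasons. The 6-month form depends on the woman sending it back, and a woman who has relapsed, feels worse or gained little may be less inclined to do so. The comparator is also a single value from an earlier trial, so no concurrent arm loses women in the same way. The primary objective covers women in real-life conditions whatever their treatment or the interval since it ended, and a mean among responders estimates something narrower.

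At stake are the size of the reported change, the planned comparison of that change with the PACThe effects, and control of the false-positive rate should the true excess over the historical value be small.

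**Working it through.** **Inputs from the documents.** N = 400; standardised effect 0.2; "alpha risk equal to 5% and 95% power"; drop-out 15–20%; planned 6-month change: "expected value of 10 points"; historical control change 4.6; SD 15–16 in the earlier trial, expected to be larger here. **Assumed:** the gap between responders and non-responders, which the documents do not give, and an SD of 20 as one larger value. The drop-out rate is read as loss at 6 months, because N is set for that endpoint.

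**1. The plan's own figure.** A one-sample t-test with effect 0.2, two-sided 5% and 95% power needs n = 327 (noncentral t). Dividing by 1 − d gives 327/0.85 = 385 at 15% loss and 327/0.80 = 409 at 20%. The stated 400 lies in that range. Power is 95.7% with 340 completers and 94.6% with 320. The allowance for drop-out therefore does its job for power.

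**2. Bias of the completer mean.** With non-response proportion d,

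bias = d × (mean change in responders − mean change in non-responders).

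With responders at 10 points:

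| Non-responders' change | Gap | Bias, d = 15% | Bias, d = 20% | True excess over 4.6, d = 15% / 20% |
|---|---|---|---|---|
| 4.6 | 5.4 | 0.81 | 1.08 | 4.59 / 4.32 |
| 0 | 10 | 1.50 | 2.00 | 3.90 / 3.40 |

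The apparent excess is 10 − 4.6 = 5.4 in every case. Smaller gaps do less: 2 points gives 0.30–0.40 and 5 points gives 0.75–1.00.

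**3. Could this reverse the conclusion at the planned effect?** For the whole-cohort mean to equal 4.6, non-responders would have to average (4.6 − 0.85 × 10)/0.15 = −26 at 15% loss, or (4.6 − 0.80 × 10)/0.20 = −17 at 20%. In the worst row of the table, the excess of 3.4 is 3.4/(16/√320) = 3.8 standard errors at SD 16 and 3.4/(20/√320) = 3.0 at SD 20.

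**4. Error rate if there is no true excess.** If the cohort mean is 4.6 and the gap is 5 points, the upper-tail error (nominal 2.5%) is 1 − Φ(1.96 − bias/SE). At SD 16:

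- 15% loss: bias 0.75, SE 16/√340 = 0.868, error 13.7%.
- 20% loss: bias 1.00, SE 16/√320 = 0.894, error 20.0%.

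At SD 20 the figures are 10.2% and 14.3%.

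**5. Scale.** The effect the study is sized for is 0.2 × 16 = 3.2 points at SD 16, so a 1-point bias is 1/3.2 = 31% of it. The plan expects 10 points against 11.9 in the earlier trial, a drop of 1.9. A bias of 1.5–2.0 points could hide most or all of that drop.

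**6. Would using the observed scores help?** Simulations assumed 400 women, true change 10, SD of change 16, correlations 0.45–0.65 between visits, and log-odds of non-response falling by 0.03 or 0.06 per point of the driver. They used baseline, end-of-stay and 6-month scores only. Ranges of the mean estimate:

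| Non-response driven by | Complete cases | Conditioning on baseline and end-of-stay scores |
|---|---|---|
| Gain during the stay | 10.8–11.7 | 10.0 |
| Change after the stay | 10.5–11.2 | 10.7–11.5 |
| Total change to 6 months | 11.3–12.9 | 10.7–11.6 |

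Observed scores remove the bias in the first case, do not help in the second, and remove part of it in the third.

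**The case against.** Several parts of the opposing case stand.

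- **Direction.** Nothing in the documents shows that women who benefit less reply less. The bias is a risk of unknown size and is stated here only conditionally.
- **Size.** The 2-point figure needs 20% loss and women who attended the programme doing worse than untreated historical controls. It is an upper case, not an expectation.
- **Comparator.** The documents do not say how missing data were handled behind the 4.6. If that value also came from completers, some of the selection may be shared, and changing only this study's estimator could make the comparison less like-for-like.
- **Remedy.** A mixed model cannot correct for deterioration after the stay that is never observed.

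A reader might infer that all data from non-responders are thrown away. The documents do not support that: the exclusion stands in the paragraph on the main analysis, the general rule is partial exclusion, and the longitudinal models are separate. A reader might also see an outright contradiction between the fixed exclusion and the imputation clause. The clause can be read as a conditional follow-up, since nothing says that imputation would replace the primary test. What remains is an ambiguity: trigger, method and role are open, so the choice could be made after the data are seen. The promised assessment of missing data is a genuine safeguard.

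An imputation method or delta values may well sit in an analysis plan not shown here. That does not answer the main point, because the complete-case rule for the primary test is fixed in the article itself.

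**Conclusion.** The concern holds in conditional form. The primary test rests on responders only, and the expected 15–20% loss is met only by a larger N. If non-responders benefit less, the 6-month change is overstated by 15–20% of the gap: 0.8–1.1 points if they change by 4.6, and 1.5–2.0 points if they do not change at all, taking responders at 10.

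A reader might go further and conclude that a positive result would be an artefact of non-response. The figures do not support this at the planned effect: the excess stays at 3.0 standard errors or more in the extreme case, and erasing it would take mean falls of 17 to 26 points among non-responders. The damage is to the estimate, to its comparison with the PACThe effects, and to error control when the true excess is near zero. The 10–20% error rates require both a zero true excess and the assumed 5-point gap.

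The responder/non-responder gap, the SD of 20 and the simulation settings are assumptions. The exclusion rule, the loss rate and the absence of a concurrent arm come from the documents.

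**What to change.** Before the analysis begins:

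1. Take the primary 6-month change from the mixed model already planned, including every woman with a baseline score and using at least the baseline, end-of-stay and 6-month scores. Compare that contrast with 4.6. The 12- and 18-month scores can be left out so that the primary result is not delayed.
2. Keep the complete-case t-test as a sensitivity analysis.
3. Prespecify a delta-adjusted analysis, for example with non-responders' mean change set to 4.6 and to 0, because the mixed model corrects only non-response explained by observed scores.
4. Keep the assessment of missing data in Data management and monitoring, but state that any imputation is a prespecified sensitivity analysis and not a later substitute for the primary method.

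The cost is a change of wording and a little more analysis, with no new data. The primary estimate would rely on missing-at-random, which the delta analysis probes. If the historical 4.6 was itself based on completers, the complete-case result kept under step 2 is the closer match and should be reported beside the primary estimate.

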Traditionally, programs in thermal resorts have been contraindicated for cancer patients during progression. However, during periods of complete remission, thermal programs can be a beneficial complementary therapy [9].

The “PACThe” program (Program of Accompanying women after breast Cancer treatment completion in Thermal resorts) enabled women treated for breast cancer (severe forms having received chemotherapy, surgery, radiotherapy) and in complete remission to be cared for in thermal establishments on a full-board dietary basis. The objectives of the program were to improve the patients’ quality of life by restoring their functional capacities, ensuring efficient weight control, combating stress and compensating for social and socio-aesthetic handicaps. To this end, the program combined hydrothermal balneotherapy, adapted physical activity, nutritional and dietary education, socio-aesthetic advice and psychological follow-up.

The program’s impact was evaluated at one year in a randomized controlled trial involving 251 patients (number calculated according to the assigned objective of improvement in the primary endpoint) [1]. This trial was complemented by an ancillary medico-economic study that was published separately [10]. A third study assessed quality of life (the study’s primary endpoint) at five years in surviving patients [2].

The results at one year show that implementation of the program is statistically significantly associated with an improvement in the following elements: quality of life measured with the SF36 QoL scores [3] at 6 and 12 months and compared between the “SPA group” and the “control group”; functional capabilities; weight control, particularly in overweight patients; depressive situation; sleep; level of physical activity in previously active patients; and return to work [1].

The intervention proved to be cost-effective at one year for all program participants and at six months for women who had returned to work. The main difference was in the use of physiotherapy, which was higher for patients in the control group [10].

At five years, the significant difference in quality of life was maintained between the two groups (*p* =.009 with a delta of 7.2 in the SF36 QoL score [3]), while mortality rates did not differ.

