#### Secondary objectives and outcomes measure

The secondary objectives are to assess the effectiveness of the PACThe program in real-life conditions based on subgroups and to compare the observed effects (at various time points) with those observed in the original PACThe study at the same time points.

Secondary endpoints will be assessed with the SF-36 questionnaire global and subscale scores obtained at inclusion, end of program, 6, 12 and 18 months after end of program. Scores in subgroups (according to BMI, age, menopausal status, level of education, precariousness (assessed via EPICES score)) will also be assessed.

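### Secondary and subgroup effects are defined as uncontrolled changes from baseline, which cannot support the stated aim of programme effectiveness

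*Protocol article*

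**What the plan says.** Under Statistical analysis, the protocol article states that "Confidence interval estimates of observed effects (changes in measurements at different time points post-program vs. baseline) will be used for comparison with the effects" that PACThe found. The same sentence extends this to subgroups: "as well as analysis in subgroups defined by age, menopausal status and type of anti-cancer treatment". The parenthesis in that sentence fixes what an observed effect is: the cohort's own change from baseline, with nothing subtracted.

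Under Secondary objectives and outcomes measure, the aim served by this analysis is to "assess the effectiveness of the PACThe program in real-life conditions based on subgroups"; the other secondary aim is a comparison with PACThe at matching time points. The Background section states the aim in the same terms.

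The main analysis is built differently. It tests the 6-month change in SF-36 global score against the change in PACThe's control group, used as a historical comparator. The Sample size section gives the PACThe figures: a "difference between 6 months and baseline of 11.9 points in the experimental group, and 4.6 in the control group", with between-group differences of 2.2 points at baseline and 9.5 points at 6 months. It expects a change of 10 points in the present cohort.

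**The concern.** A change from baseline in a single arm combines the programme's contribution with everything else that moves the score over the same months: recovery after treatment, regression to the mean, and other care. The plan recognises this for its primary test, which uses the PACThe control change as the reference rather than zero. It assigns no such reference to the end of the programme, 12 months, 18 months or any subgroup, yet it describes the subgroup aim as effectiveness.

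The subgroups are where this matters most. The cohort admits women regardless of treatment and of time since treatment, and type of anti-cancer treatment is one of the subgroup factors. Background recovery may well differ by treatment and age. If it does, subgroups with the same programme benefit will show different raw changes, and the plan offers nothing to tell the two sources apart. At stake is a published statement that the programme works better in one kind of patient than in another.

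**Working it through.** **Inputs.** All from the Sample size section unless marked.
- PACThe 6-month change: 11.9 experimental, 4.6 control.
- PACThe between-group difference: 2.2 at baseline, 9.5 at 6 months.
- Expected change in this cohort: 10.
- N = 400, drop-out 15–20%, effect size 0.2, alpha 5%, power 95%.
- SD: 15 to 16 in PACThe, without saying whether of scores or of changes. It is expected to be larger here, but no figure is given. I use 16, 20 and 27 as a range; 27 is an assumption, the value at which 5.4 points is an effect size of 0.2 (5.4 / 0.2).

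**The plan's own figure.** One-sample t-test, two-sided 5%: ((1.960 + 1.645) / 0.2)² = 324.9, or 327 evaluable by the noncentral t. Inflated, 327 / 0.85 = 385, 327 / 0.82 = 399 and 327 / 0.80 = 409. The stated 400 is reproduced, and the sample size is not at fault on this point.

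**Net effect in PACThe.** 11.9 − 4.6 = 7.3, which agrees with 9.5 − 2.2 = 7.3.

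**Background share of a raw change at 6 months.** 4.6 / 10 = 46% of the change expected here; 4.6 / 11.9 = 39% of the PACThe experimental-arm change. Net of control, the expectation here is 10 − 4.6 = 5.4.

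**What a programme with no effect would show.** Suppose the true change is 4.6 throughout. The 95% interval is 4.6 ± t × SD / √n, and the chance that it excludes zero comes from the noncentral t with parameter 4.6√n / SD. I take n = 320 (400 less 20%); the subgroup sizes are assumed.

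| SD | 95% CI, n = 320 | excludes 0, n = 320 | n = 160 | n = 80 |
|---|---|---|---|---|
| 16 | 2.8 to 6.4 | 99.9% | 95% | 72% |
| 20 | 2.4 to 6.8 | 98% | 82% | 53% |
| 27 | 1.6 to 7.6 | 86% | 57% | 33% |

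An interval for raw change that excludes zero is therefore no evidence of effectiveness, overall or in a subgroup.

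**Subgroup illustration (assumed values).** Give two subgroups the same programme gain of 5.4 and background changes of 2 and 7. Their raw changes are 5.4 + 2 = 7.4 and 5.4 + 7 = 12.4: a 5-point difference with no difference in programme effect.

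**Which PACThe figure a raw change can be set beside.** Raw against raw is 10 vs 11.9; net against net is 5.4 vs 7.3. The gap is 1.9 in both. The ratio is 84% raw (10 / 11.9) and 74% net (5.4 / 7.3). At SD 16 and n = 320, a raw change of 10 has an interval of 8.2 to 11.8. That interval contains 9.5 and lies wholly above 7.3, but neither is a raw change, so neither position says anything about agreement with PACThe.

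**The case against.** The strongest reply is that the comparison with PACThe is already raw against raw. The analysis sentence defines effects as changes from baseline, and carrying that definition across leads to the experimental-arm 11.9. The Sample size section reads the same way: it expects this cohort to fall a little short of PACThe and sets 10, which is below 11.9 but above both 9.5 and 7.3. This stands.

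A reader might nevertheless infer that the plan will put 10 beside 9.5 and claim full replication. The document does not say so, and its own figures point the other way. A reader might also note that a null programme's 4.6 is 63% of 7.3, but that divides a raw change by a net effect. The consistent figure is 39% of 11.9, which would look like a clear failure to reproduce PACThe.

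Three further points stand in part. Subtracting 4.6 from both sides leaves the 1.9-point gap unchanged, so the net form adds nothing to the question of whether PACThe's change recurs; it matters only for statements about effectiveness. The word effectiveness appears in the objectives rather than in the analysis sentence, but that sentence is the analysis given for the objective. Finally, PACThe had 251 patients over both arms, so control changes by subgroup would be imprecise and may not exist. That is a reason for calling subgroup results descriptive, not for leaving the claim as it is.

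**Conclusion.** The point holds for the secondary time points and the subgroup analyses. The quantity the plan fixes for them is an uncontrolled change, and the objective it serves is effectiveness. At 6 months the part not due to the programme is put at 4.6 of the expected 10 points (46%). This assumes that PACThe's control change carries over to a cohort with broader treatment histories. Calling it natural recovery is an interpretation, since it may include regression to the mean, but neither belongs in a programme effect. The article gives no control change for other time points or for any subgroup, so the size there cannot be computed, and the 5-point subgroup example only illustrates the mechanism.

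The primary analysis is not affected, because it is referred to the PACThe control change. The comparison with PACThe is sound if read as 10 against 11.9. What is missing there is an explicit statement, because the between-arm figures (9.5, or 7.3 net) are also in the article and are not comparable with a raw change.

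**What to change.** Amend the Statistical analysis section before the data are analysed:

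1. Name the PACThe experimental-arm change at the same time point (11.9 at 6 months) as the reference for the raw comparison, and say that agreement shows only that the within-arm change recurs.
2. For any effectiveness statement at a secondary time point, report cohort change minus PACThe control change at that time, where PACThe has one, beside PACThe's net effect. At 6 months the matching figures are 5.4 expected against 7.3.
3. Report subgroup results as descriptive change from baseline. Do not interpret them as effectiveness, or as a difference in effect, unless a PACThe control change for the same subgroup is available. Align the wording of the secondary objective with this.

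The cost is analysis wording, plus retrieval of PACThe control changes where they exist; no new patients, visits or data collection in this cohort are needed. The downside is smaller stated effects and more modest subgroup conclusions.
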